### The intervention

CPSL staff will identify village volunteers who will steer the formation of women’s SHGs in the tolas randomized to the early intervention group. Using the Rojiroti model of microfinance [15], members of the SHG will each be asked to save a small amount (Rs. 2.50 (£0.025)) every month. When required, SHG members will be able to benefit from loans from two sources: initially from their own pooled savings and, after three to six months of running the SHG, also from CPSL. Applications for loans will be made to the SHG, and the group can apply to CPSL for the funds if it cannot provide the member with the required amount. The loans can be taken for any purpose approved by the group members. The annual interest rate on a reducing balance is 18% for all loans, providing interest payments are made and at least Rs 1 (£0.01) of the principal loan (the capital borrowed) is repaid. If Rs 1 of the borrowed amount and the monthly interest are not paid, an interest rate of 24% is charged per annum. The participant seeking the loan has to specify the loan tenure when receiving the loan; in the past CPSL have recovered between 80 and 90% of the loans within this specified time [15] and ultimately 99.3% of loans are repaid. For this study, the total duration of external credit will be recorded to analyze whether this affects health outcomes.

The tolas randomized to the control arm will not receive any intervention in the initial 18 months of the study. After 18 months, CPSL staff will enter the control tolas and provide support to establish SHGs and provide microfinance in a manner similar to the process in the tolas randomized to the intervention arm.

### Outcome measures

The primary outcome measure will be the mean weight for height z-score (WHZ) of children under five years of age in the paired early and late intervention tolas at 18 months after the scheme has been implemented in the early intervention tolas.

The secondary outcome measures will be mortality rate, overall mortality, mean weight for age z-scores (WAZ) and height for age z-scores (HAZ), the prevalence of moderate to severe underweight (WAZ < −2 SD), stunting (HAZ < −2 SD), and wasting (WHZ < −2 SD) in children under five years of age, and the prevalence of moderate to severe acute malnutrition (based on MUAC between 12.5 and 11.5 cm and MUAC <11.5 cm, respectively) in children between 6 and 60 months of age [19] in the early versus late intervention tolas 18 months from the start of the study. The same outcome measures will be analyzed at 36 months to determine if the late intervention tolas ‘catch up’.

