#### Statistical tests

Using linear regression for continuous outcomes and logistic regression for binary outcomes, we will compare measurements from children in the early intervention tolas and children in the late intervention tolas at 18 months. We will use a multilevel model to account for the clustering of children within families within tolas, and include baseline measurements of the outcome and other confounders as model covariates. Tolas are being recruited in pairs within agro-economic zones. All tolas recruited thus far are in the same zone and all tolas in the feasibility and pilot study will be in this same zone. Given that tolas have not been matched on any other characteristics, we will not account for the pairing of tolas in our analysis.

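### The 36-month analysis is meant to show whether late tolas catch up, but the stated early-versus-late comparison does not by itself estimate catch-up; the change in the gap between 18 and 36 months should be reported

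*Protocol article*

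**What the plan says.** The Outcome measures section of the protocol article defines the secondary outcomes "in the early versus late intervention tolas 18 months from the start of the study", and the primary outcome likewise refers to the 18-month comparison. It then states the purpose of the later follow-up: "The same outcome measures will be analyzed at 36 months to determine if the late intervention tolas" catch up.

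The Statistical tests section is the only place where a model is described: "we will compare measurements from children in the early intervention tolas and children in the late intervention tolas at 18 months". The model allows for children within families within tolas, and will "include baseline measurements of the outcome and other confounders as model covariates". The section names no 36-month model, no term for time or for arm by time, and no criterion for catch-up.

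Under The intervention, the control tolas "will not receive any intervention in the initial 18 months of the study", and then: "After 18 months, CPSL staff will enter the control tolas and provide support to establish SHGs". From month 18 both arms are therefore exposed. The Data collection section has weight, height and MUAC measured again at 18 and at 36 months.

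**The concern.** Catch-up means that a gap present at 18 months has narrowed by 36 months, so it is a statement about change. The article pairs that question with the same between-arm measures at the later time point. A 36-month difference near zero is what catch-up would produce. It is also what would be seen if the scheme never had an effect, or if a persisting gap were hidden by sampling error.

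The direction matters. In most analyses imprecision works against the claim of interest. Here the favourable reading, that late tolas caught up, corresponds to a null result, so imprecision works in its favour. At stake is what the second 18 months of the pilot can be said to show, and what is carried into the design of the definitive trial.

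**Working it through.** The article gives no SD, ICC, effect size or significance level, and no 36-month figure, so there is nothing of its own to reproduce. The check has a logical part and an illustrative numerical part.

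**What each contrast identifies.** Take a true effect of 0.2 z and no sampling error. E and L are the mean shifts in the early and late arms.

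| Scenario | E18, L18 | E36, L36 | Gap at 18 | Gap at 36 | Gap(18) − gap(36) | Late arm's own change |
|---|---|---|---|---|---|---|
| True catch-up | 0.2, 0 | 0.2, 0.2 | 0.2 | 0 | 0.2 | 0.2 |
| No effect ever | 0, 0 | 0, 0 | 0 | 0 | 0 | 0 |
| Early benefit fades | 0.2, 0 | 0, 0 | 0.2 | 0 | 0.2 | 0 |
| Benefit grows with exposure | 0.2, 0 | 0.4, 0.2 | 0.2 | 0.2 | 0 | 0.2 |
| Gap persists, late arm gains nothing | 0.2, 0 | 0.2, 0 | 0.2 | 0.2 | 0 | 0 |

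The first three rows share a 36-month gap of zero. The change in gap separates catch-up from no effect ever. It does not separate catch-up from fading of the early arm, and it is zero when late tolas benefit while early tolas keep gaining. The within-arm changes are needed for both distinctions.

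**How weak a null result at 36 months would be.**

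Inputs from the article:
- 20 pairs, so 20 tolas per arm (Sample size and power calculations).
- About 100 people per tola (Study design).
- Bihar children aged 0-6: 18,582,229 of 103,804,637, or 17.9% (Table 1). Multiplying by 5/7 gives 12.8%, or about 13 under-fives per tola.

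Assumptions not in the article: WHZ SD 1.0 to 1.2, ICC 0.05, two-sided 5% test.

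1. SE of the gap = sqrt(2 × SD² × (1 + 12 × 0.05) / (20 × 13)). This is 0.111 for SD 1.0 and 0.133 for SD 1.2.
2. The 95% CI half-width on 38 df is 2.024 × SE, or 0.22 to 0.27 z. Even an estimate of exactly zero would not exclude a 0.2 z gap.
3. Probability of a non-significant result, from the non-central t on 38 df with non-centrality gap/SE:
   - persisting gap 0.2 z: 0.58 (SD 1.0) and 0.69 (SD 1.2);
   - persisting gap 0.3 z: 0.25 and 0.41;
   - no effect: 0.95, by construction of a 5% test.
4. Sensitivity, with SD 1, ICC 0.02 to 0.10 and 13 to 18 children per tola: a persisting 0.2 z gap is non-significant in 38 to 68% of trials.

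**Precision of the change in gap.** With r the correlation between the estimated gaps at the two times, SE(change) = sqrt(2 × SE² × (1 − r)). At the midpoint SE of 0.122 this is 0.154 for r = 0.2 and 0.109 for r = 0.6. For SD 1.0 and r = 0.5, the power to detect full closure of a 0.2 z gap is about 42%.

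**Effect of requiring a significant 18-month gap first.** With a persisting 0.2 z gap, SE 0.111 to 0.133 and r 0.2 to 0.6, simulated trials that pass such a gate show an average gap(18) − gap(36) of 0.04 to 0.12 z although nothing has closed. Without the gate the average is zero. Selecting on significance inflates the 18-month gap and so creates apparent catch-up.

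**The case against.** The strongest reply is that the article does not confine the 36-month analysis to one cross-sectional comparison. The phrase about the same outcome measures names variables, and the model for a secondary time point may sit in a fuller plan that is not shown. The 18-month comparison is also planned, so both gaps will be available. A clear 18-month gap followed by a tight near-zero 36-month gap would bear directly on catch-up.

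Much of this stands. A reader might infer that the planned analysis cannot show catch-up at all, or that it will usually support catch-up whatever happened. The document supports neither reading. No section says that non-significance at 36 months will be taken as catch-up. On the illustrative figures a persisting 0.3 z gap would be missed in only 25 to 41% of trials. The 95% figure under no effect holds for any 5% test, and the 18-month result would usually warn that there was no gap to close.

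The numbers also rest on an assumed SD and ICC and an approximate tola size, and they ignore any gain in precision from baseline adjustment.

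What remains is that the article states both a question about change and a means of answering it, and the means is not a contrast of change. Setting a significant 18-month result beside a non-significant 36-month one does not test change, and the article gives no margin for calling the later gap closed. A fuller plan could add the right contrast, but the published statement would still need aligning with it.

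**Conclusion.** The point holds in limited form. As stated, the 36-month early-versus-late comparison is part of the answer to the catch-up question but does not answer it alone. A small or non-significant difference there cannot separate a closed gap from no gap ever. With about 20 tolas per arm it is weak evidence: on the assumptions above, a persisting 0.2 z gap goes undetected in 58 to 69% of trials, or 38 to 68% over the wider ICC and cluster-size range at SD 1.

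The importance is minor to moderate. This is a secondary analysis of a pilot whose first aim is feasibility. The 18-month primary outcome, the number of tolas and the data collection are untouched.

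**What to change.** State in the Outcome measures or Statistical tests section that catch-up will be judged by the change in the early-late gap between 18 and 36 months. Estimate it with a 95% CI from one multilevel model of both time points with an arm-by-time term, keeping the planned clustering and baseline adjustment.

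Report four things in all cases: the 18-month gap, the 36-month gap, the change in gap, and the change within each arm. The within-arm changes help to tell late-arm gain from early-arm fading. They are descriptive, since ageing or trends common to both arms also move them.

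Do not make reporting or interpretation conditional on a significant 18-month gap. Add a sentence that a non-significant 36-month difference alone is not evidence of catch-up.

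The cost is wording and one model; no new measurements are needed. The drawback is that the change in gap will be imprecise, with an SE of about 0.11 to 0.15 z under these assumptions, so the pilot's statement on catch-up will be more cautious.

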### Determining the primary outcome measure

At the initial stages of planning the study, the primary outcome measures were mortality rate among children under five years of age and the overall mortality in the tola. However, on further literature review and discussion with experts, the primary outcome was changed to the mean WHZ of children under five years of age. Given the short duration of the study and limited number of participants, the effect of the intervention on mortality rates may not be evident. WHZ is a marker of acute malnutrition and wasting (WHZ < −2 SD) is associated with a significantly increased risk of subsequent mortality. Children with severe wasting (WHZ < −3 SD) have a 9.4-fold higher chance of dying while those with moderate wasting (WHZ −3 to −2 SD) have a 3.0-fold higher chance of dying when compared with their non-malnourished counterparts [20]. These figures are higher compared to the odds ratios for mortality for HAZ and similar to the odds ratios for WAZ. We chose WHZ as the primary outcome measure as it is strongly associated with mortality and may be affected by the intervention within the short duration of the study period.

### Qualitative measures

Qualitative data on the use of loans will be collected to examine the purpose for requesting money. The analysis will evaluate whether the purpose of loans changes in the second 18-month period of the study. Experience of CPSL workers suggests that loans are initially taken to tide over emergencies. As SHGs mature, more loans are taken for income-generating activities such as buying livestock.

### Sample size and power calculations

The data collected as part of this pilot study will be used to inform sample size calculations for a future definitive cluster RCT, using the methods described by Hayes and Bennett [21]. Published estimates of nutrition in Bihar date back to 2006 and suggest that 55% of under fives in Bihar are underweight (61% of children from scheduled castes) [22]. The pilot study will provide a current estimate of the prevalence of mortality and malnutrition in our study population.

The study will be initiated in 10 pairs of tolas to test the feasibility of recruitment, randomization, and data collection. When this is established, another 10 pairs of tola will be recruited to complete the pilot phase of the study. Based on local estimates of tola population and number of children under five years of age in each tola, 20 pairs of tolas will be sufficient to allow a power calculation to determine the sample size required to detect a statistically significant effect of Rojiroti microfinance on the primary outcome measure.

### Randomization and blinding

The 10 pairs of tolas for the feasibility phase were selected by the CPSL staff and tola names converted into code numbers which were provided to the research team based at the University of Nottingham. The code numbers were randomly assigned to either early or late intervention by the researchers in Nottingham who were blind to intervention allocation. This information was transferred back to the research team in Patna and the CPSL staff who matched the randomly assigned allocations to the tola name prior to baseline data collection. The researchers in Nottingham who will perform data analysis will remain blind to the tola allocation; however it is not possible to blind the CPSL staff and participants as the formation of SHGs and provision of microfinance cannot be masked. A further 10 pairs of tolas will be similarly randomized to complete the pilot phase of the trial.

### Data collection

Basic demographic information about each participating tola will be collected at the beginning of the study (Table 2). Information about each participating mother and her child and/or children under five-years-old will be collected using standard questionnaires. Data collected will include immunization rates among the participating children and whether they have a ‘Road to Health Card’ [23]. The Road to Health Card is a record of immunization and growth of a child. It is given to the mother when the child is born and is used to monitor child health until five years of age. Additional information about the mothers such as ability to read and write, years of schooling, freedom to travel without permission, and whether they have needed to sell assets in an emergency will also be collected. All questionnaires have been prepared in Hindi and will be communicated to the participants by researchers who can speak both Hindi and Magadhi, the local dialect of Hindi spoken in the region.

**Table 2 Tab2:** **Data collected at baseline survey**

**Tola level information** (Collected from village volunteer)	How many houses are there in this tola?
	How many people live in this tola?
	How many children under 5 years of age live in this tola?
	How many children were born in the last 1 year?
	How many people have died in the last 1 year?
	How many children under 5 years of age have died in the last 1 year?
**Information about mothers** (Collected from mother)	How old are you?
	Can you read and write?
	Have you ever been to school?
	How many under children under 5 years old do you have?
	Do you or your family own any land?
	Have you or your family had to sell any assets due to emergencies such as money required for medical treatment in the last 1 year?
	Can you travel outside the village without permission from your family?
**Information about children** (Collected from mother)	Age
	Gender
	Has the child received any immunization?
	Does the child have a Road to Health card?
	Was the child born at home?

The age, weight, height, and MUAC of each child under five years of age will be recorded for all children in the tola, irrespective of whether their mothers are in the SHG. The measurement will be performed by CPSL field workers. Two workers will work together to weigh and measure each child and record the measurement that both agree on. Standing height in children aged two years and older will be measured with Seca 213 Portable Stadiometer (Seca, Birmingham, UK) to the closest 1 mm. The length of younger children will be measured using Seca 210 Measuring Mat (Seca, Birmingham, UK). Weight will be measured with Libra Fitness Standing Scale (Edryl, Goa, India); younger children will be weighed in hanging scales (Venus CHS, Ace, Rajasthan, India) and smaller infants and newborns on Docbel (Braun) Baby Scales (Popular, Docbel Industries, New Delhi, India). All weights will be recorded to the closest 100 g. MUAC will be measured and recorded to the closest 1 mm using MUAC tapes provided by the UNICEF Supply Division. CPSL staff will determine and record the number of children under five years of age who have not been measured (such as children who are temporarily absent from the village and those who are ill). This will be determined by asking the village volunteers and the mothers if they know of any children who are absent.

In addition, the village volunteer will estimate the total population, the population under five years of age, and the number of deaths in the last year (overall mortality and deaths among children under five years of age) in the tola. This information will collected using a standard questionnaire.

After 18 months, all the participating children will be reweighed and re-measured and data regarding overall mortality and mortality among children under five years of age during the study period in the tola will be collected. The CPSL-supported SHGs will then be introduced into the late intervention tolas. After 36 months from the start of the study children’s weights, heights, and MUACs will be recorded again, together with mortality data, in all tolas. At 18 and 36 months, data on deaths in each tola in the preceding 18 months will be requested from the state government (Registration of Births and Deaths) and will be used to check the validity of the mortality data obtained from questionnaires.

### Data management

Tola information and individual participant information will initially be recorded on paper questionnaires by CPSL research staff and subsequently entered into electronic data sheets by the research team in Patna and transferred to the University of Nottingham in secure password-protected files. The original data sheets will be scanned and electronic copies will be retained by the research team in Nottingham while the original papers will be retained by the team in Patna. All electronic and paper records will be filed in numerical order and stored on a secure server accessible to the research team. The electronic records will be regularly backed up the University of Nottingham.

### Evaluating the accuracy and completeness of data collection

The electronic data sheets (Excel 2007; Microsoft Corporation, Redmond WA, USA) have data validation limits set such that potentially spurious weights, heights, and MUACs will be flagged up at the time of data entry and can be rechecked against the paper records. Concordance between paper records and data entered into the electronic data sheets will be verified again by the researchers in Nottingham. A 10% random sample of all paper records will be checked against the electronic records. The Emergency Nutrition Assessment Tool [24] will be used to further check the data recorded in the electronic data sheets for spurious age, height, and weight entries such as a recorded height too small for the recorded age; any entry flagged as suspicious will also be re-checked against the paper records and any errors in data entry corrected. If any spurious data remain, we will conduct a sensitivity analysis for each of our outcome measures, excluding children with a spurious age, height and/or weight record.

### ‘Viral’ spread of self-help groups

Previous experience of CPSL in the region indicates that once SHGs begin in some tolas, information spreads by word of mouth through relatives and women in nearby tolas often set up their own SHGs (‘viral’ spread). In this trial, paired early and late intervention tolas will be at least 15 km apart in order to minimize viral SHGs being set up in the late intervention tolas. To monitor viral spread in this study, a local survey by CPSL staff will determine how often nearby tolas set up SHGs. The socioeconomic characteristics of group members in SHGs which formed virally will be compared with those of women in groups formed by CPSL. Where possible, consent for the collection of health outcome data will be taken and these data will be collected in the viral tolas similar to the data collection in the randomized tolas. CPSL staff will also record whether tolas assigned to the late intervention arm proceed regardless and set up their own SHGs during the first 18 months of the study.

### Statistical analysis

#### Type of analysis

In the feasibility and pilot study and any future trial, intention-to-treat analysis will be used, that is, where a tola has been randomized to receive microfinance early or late, their data will be included irrespective of whether the SHG and microfinance have run successfully or whether the tolas in the late intervention group formed SHGs through viral spread prior to their designated time.

#### Statistical tests

Using linear regression for continuous outcomes and logistic regression for binary outcomes, we will compare measurements from children in the early intervention tolas and children in the late intervention tolas at 18 months. We will use a multilevel model to account for the clustering of children within families within tolas, and include baseline measurements of the outcome and other confounders as model covariates. Tolas are being recruited in pairs within agro-economic zones. All tolas recruited thus far are in the same zone and all tolas in the feasibility and pilot study will be in this same zone. Given that tolas have not been matched on any other characteristics, we will not account for the pairing of tolas in our analysis.

#### Planned exploratory analyses

The feasibility and pilot phase will explore whether data can be collected on maternal literacy and years of schooling women have received. If adequate data are available, we will compare the effectiveness of the intervention according to whether the mother was literate or illiterate and whether she had received any years of schooling.

